### Study design

The study design concerns a two-arm randomized controlled trial, evaluating the effects of an emotion regulation training intervention versus a care-as-usual control group. Assessments in the two conditions are planned at four time points: after recruitment (T0), before the start of the intervention (T1), after the end of the intervention (T2), and at 6-months’ follow-up (T3). Primary outcome measures are emotion regulation and eating behavior, more specifically emotional eating. As secondary outcome measures, (1) weight change, (2) psychological well-being, and (3) sleep quality will be taken into account.

After giving informed consent (T0), participants and their parents will fill out questionnaires assessing the psychological well-being, ER capacities, and perceived stress of the child (parent- and self-report), which will be used for descriptive purposes or as covariates. Next, before the start of the intervention (T1), at the end of the intervention (T2), and at 6 months’ follow-up (T3), participants will fill out questionnaires on their psychological well-being, sleep quality, ER capacities, eating behavior, and perceived stress level, and they will participate in a stress paradigm. On top, at T1, the participants will also complete the Standard Progressive Matrices test to determine their overall cognitive ability. Parents of the participants will be asked again to fill out questionnaires on the psychological well-being and the eating behavior of their child at T2 and T3. Moreover, the participants in the intervention condition will be asked to fill out a diary three times a week on their stress level, affect, ER capacities, and emotional eating behavior between the ER training sessions. Filling out a diary enables a more momentary inspection on the relationship between the stress level, ER capacities, and emotional eating behavior in the naturalistic environment of the participants.

The eligibility, allocation, and assessments are illustrated in Figs. 2 and 3.

**Fig. 2 Fig2:**
[figure not shown]
Process of eligibility, allocation, and assessments

**Fig. 3 Fig3:**
[figure not shown]
Overview of enrolment, allocation, interventions, and assessments

### Randomization

Stratified randomization is a two-stage process, used to control for the influence of covariates (baseline characteristics), in the randomization process [135]. In the current RCT study, both sex and age are identified as potential and important covariates. Therefore, separate blocks for each combination of the covariates will be generated (e.g., girls 10–12, boys 10–12, girls 13–14, and boys 13–14).

Participants who give consent to participate the study will be assigned to one of the four blocks.

Afterward, simple randomization to one of two conditions (e.g., experimental vs. care as usual condition) will be applied within each block at the individual level using dice [82]. The dice is thrown by the same researcher in all consecutive waves. Based on our a priori power calculations that 140 participants have to be included, we will recruit participants until each of the blocks has 35 participants.

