#### Analytical plan

To solve the problems of noncompliance and missing outcomes, which are iterative complications in an RCT study, the intention-to-treat (ITT) principle will be used [69]. Multilevel analyses will be used to test the treatment effects, allowing handling of the missing and nested data from the two conditions (intervention versus control condition). More specifically, mixed models with fixed effects for condition (intervention versus control condition), time (immediately after intervention and 6 months’ follow-up), and their interaction, adjusted for baseline will be used.

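### Simple dice randomisation within the four sex-by-age strata balances sex and age no better than no stratification, and the stated model names neither covariate

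*Protocol article*

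**What the plan says.** The protocol article, section Randomization, gives the purpose first: "Stratified randomization is a two-stage process, used to control for the influence of covariates (baseline characteristics), in the randomization process". It adds that "both sex and age are identified as potential and important covariates". Four strata follow (girls and boys, each aged 10–12 or 13–14). The article calls them *blocks*, but they are strata, not permuted blocks.

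The allocation method comes next: "simple randomization to one of two conditions (e.g., experimental vs. care as usual condition) will be applied within each block at the individual level". It is done with dice, and "The dice is thrown by the same researcher in all consecutive waves". No restriction within strata, such as permuted blocks or minimisation, is described. On numbers, "we will recruit participants until each of the blocks has 35 participants", which gives 4 × 35 = 140. The section Sample size plans 70 per condition.

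The section Analytical plan specifies "mixed models with fixed effects for condition (intervention versus control condition), time", their interaction and an adjustment for baseline. No sex, age or stratum term is named.

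**The concern.** Stratification controls a covariate only if allocation inside each stratum is restricted so that the arms stay close in size there. If every child is allocated by an independent throw, sorting children into strata beforehand changes nothing in the distribution of the result. The section therefore claims a property that the method it describes does not have.

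Two things are at stake. First, the arms can differ by chance on covariates that the plan itself considers important. If sex is related to an outcome, the arm contrast shifts by the imbalance times the sex difference in that outcome, so a 10-point imbalance passes on one tenth of that difference. Second, the usual remedy for such an imbalance is to put the covariates in the model, and the model as printed does not name them. The equal split of 70 and 70 is also not secured.

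**Working it through.** **Inputs.** Four strata of 35 children, 140 in total, simple allocation (Randomization); 63 per arm for 80% power at .05, raised by 10% to 70 per arm (Sample size). I take the throw as 1:1, so p = 0.5.

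**The plan's own figure.** The difference is 0.5. The article gives no SD, so I assume SD = 1 and a two-sided test:
- n per arm = 2 × (1.96 + 0.842)² / 0.5² = 62.8, so 63, as stated; power at 63:63 is 80.1%.
- Drop-out: 63 / 0.9 = 70, as stated.

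**Balance on sex.** Let g and b be the numbers of girls and boys in the intervention arm, with 70 of each sex in the trial. With arms near 70, the difference in the proportion of girls is about (g − b)/70.
- *As written, simple within strata.* Each stratum contributes variance 35 × 0.25 = 8.75, so four contribute 35. SD = √35 / 70 = 0.085, or 8.5 points. Simulation also gives 8.5.
- *Simple, no strata.* Simulation gives 8.5 points.
- *Permuted blocks of 4 within strata (illustration only).* Eight full blocks place 32 children evenly. The last three split 2:1, so each stratum is 18:17 and contributes variance 0.25. SD = √(4 × 0.25) / 70 = 0.014, or 1.4 points. The maximum is (36 − 34)/70 = 2.9 points, and arm totals stay within 68 to 72.

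The chance of a difference of at least 10 points in the proportion of girls is 27.2% as written and 27.4% with no strata. The chance of at least 10 points on sex or on age band is 46.9%.

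**Balance within strata, X ~ Binomial(35, 0.5).**

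| Split or worse | One stratum | At least one of four |
|---|---|---|
| 22:13 | 17.5% | 53.8% |
| 23:12 | 9.0% | 31.3% |
| 24:11 | 4.1% | 15.4% |

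The last column is 1 − (1 − p)⁴. For 23:12, with p = 0.0895, it is 1 − 0.9105⁴ = 0.313.

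**Arm totals, X ~ Binomial(140, 0.5).** P(exactly 70:70) = 6.7%. P(80:60 or worse) = 10.8%.

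**Power cost of unequal arms.** Power = Φ(0.5/√(1/n₁ + 1/n₂) − 1.96), with 126 analysed:
- 63:63 gives 80.1%
- 57:69 gives 79.8%
- 52:74 gives 78.9%, a loss of 1.2 points.

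**The case against.** **For the plan.** Simple randomisation is valid and unbiased, and it is the least predictable scheme there is. The arms balance in expectation. Adjusted BMI is expressed relative to norms by age and gender, and waist circumference is converted to z-scores for the same reason, so sex and age are largely handled for those outcomes. The Control variables section has an open list of examples, the baseline adjustment could be read to include baseline characteristics, and a full covariate list is often left to an analysis plan, which is not shown here.

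All of this stands, and it limits the point. The modelling gap is one of stated text, and it concerns mainly emotion regulation and emotional eating, for which the article plans no such standardisation. It does not answer the main point: the allocation method is stated outright, not left out, and it does not do what the same section says it is for.

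**Stronger readings that the document does not support.**
- *Allocation is not concealed.* The Procedure section places allocation after consent, and a die cannot be foreseen. The article describes no safeguard against a repeated throw, but such detail is commonly left to the full protocol.
- *An arm below 63 loses power.* One arm starts below 63 with probability 20.5%, but the other arm is then larger. A 62:78 split gives 0.5/√(1/62 + 1/78) − 1.96 = 0.98, or 83.6% power, above the 80.1% at 63:63.
- *Filling each stratum to 35 turns away a set number of children.* The article gives no stratum shares at intake, so no number follows.
- *Adjustment would raise the planned power by a stated amount.* The power calculation is for adjusted BMI, which is already normed for age and sex.

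**Conclusion.** The point holds as a contradiction between a stated purpose and a stated method. Unrestricted allocation within strata gives the same chance imbalance on sex and age as no stratification, about six times the SD reached with permuted blocks (8.5 against 1.4 points). The planned 70 per arm is not secured.

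The consequence is moderate. There is no bias on average, tests remain valid, and the power cost is about one point. What is lost is the covariate control that the section promises, with no named model term to replace it for the primary outcomes.

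The figures assume a 1:1 throw, strata filled to 35 as stated, SD = 1 for the power values, and blocks of 4 as the comparison. Other block sizes would change the 1.4 somewhat, but not the comparison between stratified and unstratified dice.

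**What to change.** 1. For the remaining waves, replace the dice with a computer-generated list of permuted blocks of varying size within the four strata. Prepare it before enrolment and keep it inaccessible to the enrolling researcher. Use a separate word for strata, so that *blocks* is not read two ways.
2. Add sex and age band as fixed effects to the mixed models in the Analytical plan, at least for emotion regulation and emotional eating.

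The required sample size does not change. The cost is a short program, someone to hold the list, and two model terms. Restricted allocation is slightly more predictable than dice; varying the block sizes limits this. Children already allocated cannot be rebalanced, so the first change helps only waves still to come. The second helps whatever the stage of enrolment.

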##### Structure

The EuREKA training consists of 12 sessions, one session of 2 hours per week. Participants will be divided in groups of five youngsters, based on their age. The choice for homogenous groups, based on age, has the following reasons: (1) the adjustment of the language during psycho-education and exercises is easier when all children have the same age, and (2) the examples can be more life phase oriented. During every EuREKA session, two trainers will be present: one trainer will focus on the content of the program, while the second trainer will monitor the process in the group (e.g., group dynamics, time management). Every EuREKA session is organized in the same structure to promote predictability and safety. First, every session starts with a short recapitulation of the previous session in which the learned competence and the accompanying homework are discussed. Second, the new competence is introduced and placed into the sequence, positioned on the previous learned competences. Third, the new competence is learned in depth, which is the biggest part of the training session, with psycho-education and exercises on the new skill. Fourth, all learned competences until that session are exercised in the sequence by an imagination exercise. Fifth, the homework of that specific session is explained, and the participants receive a little incentive for their cooperation and motivation during the session (see below, motivational processes).

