### Data analysis

#### Sample size

To detect a clinically relevant treatment effect in both primary and secondary treatment outcomes, the power analysis was conducted on the AdjBMI index [80]. To detect a minimally important difference in the in AdjBMI-index (− 0.5 BMI points), a power analysis showed that 63 participants in every condition are necessary to obtain a power of 80% at a significance level of .05. As drop-out rates are high in inpatient treatment centers [132], we will include 10% more participants. This calculation leads to the inclusion of 70 participants in both the intervention and control condition.

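### The stratified randomisation said to control for sex and age uses unrestricted dice within each stratum, so it gives no between-arm balance on either factor

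*Protocol article*

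**What the plan says.** All of the following is in the protocol article.

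- **Randomization, purpose.** Stratification is described as "used to control for the influence of covariates (baseline characteristics), in the randomization process", and "both sex and age are identified as potential and important covariates".
- **Randomization, strata.** To that end "separate blocks for each combination of the covariates will be generated": girls and boys, each aged 10–12 or 13–14. These so-called blocks are strata, not permuted blocks.
- **Randomization, allocation.** Within each stratum the method is "simple randomization to one of two conditions", which "will be applied within each block at the individual level using dice". No block size, cap, urn or minimisation rule is given. The only restriction is on recruitment, which continues until each stratum holds 35 children.
- **Sample size.** The calculation leads to "the inclusion of 70 participants in both the intervention and control condition".
- **Analytical plan.** The mixed model has fixed effects for condition, time and their interaction, and is adjusted for baseline. Sex and age are not named.

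**The concern.** Stratification balances a covariate between arms only if allocation inside each stratum is restricted in some way. Here the text states the opposite: each child is allocated by an independent throw. Sorting children into cells before throwing does not change the probability of any pattern of assignments. The property claimed for the design, control of sex and age through the randomisation, is therefore not delivered by the procedure described.

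At stake is chance imbalance on two factors that the authors themselves call important. It matters mainly for outcomes that are not standardised for age and sex: the emotion regulation and emotional eating measures and the stress paradigm, all listed as primary. The Control variables section notes that pubertal development affects stress regulation through the cortisol axis, so an age imbalance is plausibly relevant to that paradigm.

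**Working it through.** **Inputs.** Four strata of 35 (Randomization); 63 evaluable and 70 included per condition, with 10% added for drop-out (Sample size). Assumptions: fair, independent throws with probability 0.5, and the 0.5 in the sample size section read as 0.5 SD, since no SD is given.

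**The plan's own figures.** n per arm = 2(z₀.₉₇₅ + z₀.₈₀)² / 0.5² = 2(1.960 + 0.842)² / 0.25 = 62.8, so 63. Then 63 / 0.9 = 70 per arm, and 2 × 70 = 4 × 35 = 140. The figures reproduce on that reading.

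**Balance on sex.** With 70 girls and 70 boys, the SD of the between-arm difference in the proportion of girls is about √[0.25(1/70 + 1/70)] = 0.085. Simulation (400,000 trials with strata, 100,000 without) gives:

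| | Dice within strata | Dice, no strata |
|---|---|---|
| SD of difference in % girls | 8.5 points | 8.5 points |
| Difference of 10 points or more | 27% | 27% |
| Difference of 15 points or more | 7.7% | 7.7% |
| SD of difference in arm size | 11.8 | 11.8 |

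The share of children aged 10–12 behaves the same way under dice within strata (SD 8.5 points; 10 points or more in 27%).

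**Comparison with a restricted scheme.** With permuted blocks of 4, 35 = 8 × 4 + 3, so each stratum splits 17/18. The worst case for sex is both girls' strata splitting 18/17 and both boys' strata 17/18: 36/70 − 34/70 = 2.9 points. Arm sizes then lie between 68 and 72.

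**Arm size under dice.** From Binomial(140, 0.5), an exact 70/70 split has probability 6.7%, and the central 95% range for one arm is 58 to 82.

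**Power cost of unequal arms.** Power ≈ Φ(0.5 / √(1/n₁ + 1/n₂) − 1.96), with 126 evaluable after 10% drop-out:

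- 70/70, so 63 and 63 evaluable: 0.5 / 0.178 − 1.96 = 0.85, power 80.1%
- 64/76, so 57.6 and 68.4: power 79.8%
- 58/82, so 52.2 and 73.8: 0.5 / 0.181 − 1.96 = 0.80, power 79.0%

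The loss is about one point even at the edge of the 95% range.

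**The case against.** Several points limit the concern, and most of them stand.

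- **The strata do something.** Filling each cell to 35 fixes the sex and age composition of the sample, and the strata are recorded before allocation, so an adjusted analysis remains possible. The criticism reaches only between-arm balance and arm size.
- **Some outcomes are already protected.** The adjusted BMI, on which the trial is powered, is expressed relative to norms for age and gender, and waist circumference is analysed as z-scores. Baseline adjustment should also absorb part of any sex or age effect on the questionnaire outcomes. What remains is an effect of sex or age on change in outcomes that are not standardised. The documents do not allow that to be quantified.
- **An article condenses.** An unseen analysis plan may add covariates. That would limit the consequence, but the Randomization section names the within-stratum method outright, so the mismatch is in what is stated and not in what is left out. If a restriction was in fact used, the text is wrong and still needs correcting.

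A reader might infer three stronger things that the documents do not support.

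- **Bias.** Simple randomisation is valid, and chance imbalance does not bias the treatment estimate.
- **An underpowered trial whenever one arm starts below 63.** Power depends on both arms. At 62/78 the harmonic-mean size is 2 × 62 × 78 / 140 = 69.1 per arm, and at 58/82 it is 2 × 58 × 82 / 140 = 67.9.
- **Disruption of the training groups.** The Structure section says "Participants will be divided in groups of five youngsters, based on their age", but it does not tie those groups to the strata, and restricted allocation would not produce multiples of five either.

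**Conclusion.** The point holds in a limited form. The stated purpose of the stratification and the stated allocation procedure do not fit together. As written, sex and age are balanced between arms no better than under simple randomisation of the same sample: a difference of 10 points or more in the percentage of girls arises in about 27% of trials, against a maximum of 2.9 points with permuted blocks of 4. The 70/70 split is likewise left to chance.

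The harm is loss of the intended balance and some precision, chiefly for emotion regulation, emotional eating and the stress paradigm. The trial's validity is not in question. The imbalance figures rest on fair throws and full strata of 35; the power figures also rest on a difference of 0.5 SD. A correction is worth making because it is cheap, not because the design fails without it.

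**What to change.** 1. **Waves not yet allocated.** Allocate all consenting children of a wave in one run, with arm numbers balanced within stratum. Alternatively, use a concealed, computer-generated list with permuted blocks of varying size within the four strata. The 2.9-point bound applies to fixed blocks of 4. If varying blocks go up to 6, a stratum of 35 could end 19/16, and the extreme case would be 38/70 − 32/70 = 8.6 points, which needs all four strata to end that way in the least favourable directions.
2. **All waves, including those already allocated.** Add sex and age group as fixed covariates in the mixed models. The Trial status section says recruitment began in March 2018, so this is the only repair that reaches children already randomised.
3. **If dice are kept.** Describe the allocation as simple randomisation and withdraw the claim that it controls for sex and age.

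The cost is a short amendment and a few minutes to generate a list, with no extra participants. Restricted allocation is somewhat more predictable than dice, which matters in a single centre where the researchers know who is in the intervention group. Allocating a whole wave at once, or concealing and varying the block sizes, limits this.

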### Procedure

At recruitment (T0), the youngsters meeting the inclusion criteria and at least one of their parents will both receive detailed information from the researcher and the psychologists of the inpatient treatment center. After receiving this information on the study procedure orally and by letter; the youngsters and at least one of their parents will fill out an active informed consent. To obtain the target number of participants, *N* = 140 (power analysis, see below), a 2 ½ year recruitment period, March 2018 until September 2020, is necessary. After giving informed consent, participants are randomly assigned (see Randomization) to one of the two conditions: intervention condition or control condition. In the intervention condition, the ER training sessions will be given by trainers, who were also involved as clinical psychologists in the development of the ER training.

The Ethics Committee of the Ghent University Hospital approved the study design, procedure, and data collection. The national laws and the Helsinki Declaration of 1964 will be applied in all data collection procedures.

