A first strength of the study is the use of a rigorous design, including a care-as-usual control group (MOT), randomization of the participants and six-month follow-up measurements to evaluate the effect of the EuREKA-training in an inpatient treatment for obesity [56]. A second strength is the use of different measurement methods (questionnaires, stress paradigm, and physiological measures) and informants (youngsters and parents) at all four data collection time points (T0, T1, T2, and T3). A third strength is the well-evaluated ART model and training, which has been the basis for the development of the EuREKA training that will be used in this study [16, 18]. Fourth, including homework in the EuREKA training is an advantage since it has the potential to increase the feeling of competence of the learned competencies in the training sessions [76].

This study also has some limitations. First, the control group is passive, and we will be unable to control for several aspects such as extra attention, rewards, and homework in the intervention group in comparison with the control group. Second, practical obstacles are expected. Therefore, a feasibility study preceding the RCT study in an inpatient treatment center for obesity was conducted, and practical difficulties concerning the organization, such as planning the extra therapy during school hours, were taken into account. However, new unforeseen obstacles cannot always be avoided. Second, no double-blind paradigm can be used, as the researchers will know who belong the EuREKA training intervention group. A consequence is a possible contamination in the instructions by the researchers and the participants of the intervention condition trying to perform better (Hawthorne effect) [78]. However, this lack is common in educational research trials [78].

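### Each child's arm rests on a die thrown by one study researcher, so the allocation cannot be regenerated or checked afterwards

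*Protocol article*

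**What the plan says.** The protocol article, under Randomization, places each consenting child in one of four strata ("girls 10–12, boys 10–12, girls 13–14, and boys 13–14"). Simple randomization to the two arms then "will be applied within each block at the individual level using dice". The operator is named as well: "The dice is thrown by the same researcher in all consecutive waves". Keeping the thrower constant is the only control on the throw that the article describes.

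Three other places bear on the point:
- Procedure gives the order of events: "After giving informed consent, participants are randomly assigned".
- Procedure also says that eligible children and parents "will both receive detailed information from the researcher and the psychologists of the inpatient treatment center".
- The limitations in the Discussion say that "no double-blind paradigm can be used, as the researchers will know who belong the EuREKA training intervention group".

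The Discussion lists randomization among the strengths of the design.

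**The concern.** In an unblinded trial with a passive control group and many self-reported outcomes, random allocation is the main protection against the arms differing from the start. That protection is strongest when someone outside the trial team can show afterwards that each child received the arm that chance produced.

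The stated method cannot offer this. A physical throw is gone once made. What remains is at best a record of what the thrower reported, and the thrower works within the unblinded team. If a throw were repeated or its result changed, nothing described in the article would bring this to light. A positive result could then be questioned on this ground, and the sponsor would have nothing to regenerate in reply.

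**Working it through.** Most of the check is a comparison of sections. Arithmetic enters only to see whether power is affected.

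**1. Is the device random?** Yes. A fair die with half its faces assigned to each arm gives independent assignments with probability 0.5.

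**2. Can the next assignment be known before a child is enrolled?** No. Procedure puts consent before assignment, and Randomization puts the throw after placement in a stratum. Independent throws carry no information about the next one, and there is no list to consult.

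**3. Can an assignment be regenerated later?** No. A computer list with an archived seed can be rerun and compared with the arms actually given. A die cannot. A log, if one is kept, would document the reported result but could not reproduce it.

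**4. Who holds the mechanism?** One study researcher, in every wave. Procedure has a researcher informing families, and the Discussion says that the researchers know who is in the training arm. The article does not say whether the thrower also recruits, trains or assesses.

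**5. Does the die harm power?** Inputs from Sample size: difference 0.5, power 80%, significance level .05, 63 per arm, 10% added for drop-out, 70 per arm. The article gives no SD and no sidedness. I take SD = 1 and a two-sided test.

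- Reproduction: n = 2 × (1.960 + 0.842)² × SD² / 0.5² = 2 × 7.85 / 0.25 = 62.8, so 63 per arm. Then 63 / 0.9 = 70, and 2 × 70 = 140 = 4 × 35. The plan's figures reproduce.
- This depends on the SD: 0.8 gives 41 per arm, 1.2 gives 91, 1.5 gives 142 and 2 gives 252.
- With 140 fair throws, the number in one arm follows Binomial(140, 0.5), with a central 95% range of 58 to 82. After 10% drop-out that is about 0.9 × 58 = 52 and 0.9 × 82 = 74.
- Power = Φ(0.5 × √(n₁n₂ / (n₁ + n₂)) − 1.960):

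| Split of 126 | Power |
|---|---|
| 63 / 63 | 80.1% |
| 58 / 68 | 79.9% |
| 53 / 73 | 79.1% |

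A split near the edge of the range costs about one percentage point, so the sample size is not the issue.

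**6. Can the bias be sized?** No. That would need the share of throws altered and the prognosis of the children concerned. The article gives neither, and nothing in it says that any throw has been or will be altered.

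**The case against.** The case on the other side is strong on several counts.

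- **Concealment.** A reader might infer that allocation is not concealed. The documents do not support this. Consent comes first and the throw is unpredictable, so nobody can choose whom to enrol by knowing the next arm. The Discussion's remark on researchers' knowledge concerns blinding after allocation. This objection stands in full.
- **Roles.** A reader might infer that the thrower also recruits, trains or assesses. The article does not say so, and Procedure names the trainers separately from the researcher. This stands too.
- **A motive to re-throw.** Under Structure, "Participants will be divided in groups of five youngsters, based on their age", and a reader might see in this a reason to move a child to fill a group. The article mentions no re-throwing, does not forbid groups of another size, and does not tie the groups to the randomization age bands. Simple randomization from a computer list would produce the same uneven counts. The motive is conjecture and forms no part of this point.
- **Condensed article.** Logs, witnesses and separation of roles may be in a full protocol, and the figures on allocation are not shown. This stands for those details. It does not remove the core, because the article does not merely leave the method out: it names the device and the operator. An independent seeded list would be a different method.
- **Outcomes.** Cortisol, respiratory sinus arrhythmia and a computerized food-choice task stand beside the questionnaires. They reduce reporting bias. They would not protect against arms that differ in prognosis because assignments had been altered.

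**Conclusion.** The point holds as one of protection and verifiability. As described, the assignment is random and unpredictable, but it is produced within an unblinded team by a device that leaves nothing to rerun, with no described safeguard that would reveal a repeated or altered throw.

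It does not show that allocation was foreseeable, that anyone has a reason to re-throw, or that the results would be invalid. No size of bias follows from the documents. The loss of power from uneven arms is about one percentage point at a 53/73 split, assuming SD = 1, a two-sided test and 126 evaluable children. The change is worth making because the better method is cheap and recruitment was open when the article was written.

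**What to change.** For all remaining waves, replace the die with a computer allocation from a recorded seed, stratified by the existing four sex-by-age strata. It should be run by a person not involved in recruitment, training or assessment. The run takes place once consent and stratum have been logged for every child in the wave, and the seed, program and output are archived with a date. Children already allocated keep their arm, and the trial report should state which waves used which method.

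Neither the strata nor the choice of simple randomization within them has to change for this purpose.

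The cost is a short amendment and a little staff time per wave. Families learn the arm only when the wave is complete. Since Participants places recruitment four months before inpatient treatment starts, that wait should be manageable. How many waves can benefit is not clear, because Participants and Procedure end recruitment in September 2020 and Trial status in September 2019.
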